## Abstract

**Background:**

The purpose of the FABO-study is to evaluate the effect of family-based behavioral social facilitation treatment (FBSFT), designed to target children’s family and social support networks to enhance weight loss outcomes, compared to the standard treatment (treatment as usual, TAU) given to children and adolescents with obesity in a routine clinical practice.

**Methods:**

Randomized controlled trial (RCT), in which families (*n* = 120) are recruited from the children and adolescents (ages 6–18 years) referred to the Obesity Outpatient Clinic (OOC), Haukeland University Hospital, Norway. Criteria for admission to the OOC are BMI above the International Obesity Task Force (IOTF) cut-off ≥ 35, or IOTF ≥ 30 with obesity related co-morbidity. Families are randomized to receive FBSFT immediately or following one year of TAU. All participants receive a multidisciplinary assessment. For TAU this assessment results in a plan and a contract for chancing specific lifestyle behaviors. Thereafter each family participates in monthly counselling sessions with their primary health care nurse to work on implementing these goals, including measuring their weight change, and also meet every third month for sessions at the OOC. In FBSFT, following assessment, families participate in 17 weekly sessions at the OOC, in which each family works on changing lifestyle behaviors using a structured cognitive-behavioral, socio-ecological approach targeting both parents and children with strategies for behavioral maintenance and sustainable weight change.

Outcome variables include body mass index (BMI; kg/m^2^), BMI standard deviation score (SDS) and percentage above the IOTF definition of overweight, waist-circumference, body composition (bioelectric impedance (BIA) and dual-X-ray-absorptiometry (DXA)), blood tests, blood pressure, activity/inactivity and sleep pattern (measured by accelerometer), as well as questionnaires measuring depression, general psychological symptomatology, self-esteem, disturbed eating and eating disorder symptoms. Finally, barriers to treatment and parenting styles are measured via questionnaires.

**Discussion:**

This is the first systematic application of FBSFT in the treatment of obesity among youth in Norway. The study gives an opportunity to evaluate the effect of FBSFT implemented in routine clinical practice across a range of youth with severe obesity.

**Trial registration:**

ClinicalTrails.gov NCT02687516. Registered 16th of February, 2016

**Electronic supplementary material:**

The online version of this article (doi:10.1186/s12889-016-3755-9) contains supplementary material, which is available to authorized users.

## Background

There has been a global increase in the prevalence and severity of overweight and obesity amongst both adults and children [1, 2]. The World Health Organization (WHO) states that childhood obesity is one of the most serious public health challenges of the 21st century [2].

Childhood obesity is associated with a wide array of negative health consequences such as psychosocial problems, obstructive sleep apnea, increased cardio-metabolic risk and Type 2 Diabetes [3–5], resulting in considerable burden for the individual child as well as socio-economic consequences [6, 7]. In addition, childhood obesity has great impact on adulthood, and is associated with adult obesity [8] and all-cause mortality in adulthood [9]. A recent study [9] with 2.3 million participants between the ages of 16 and 19 years found that a graded increased risk for cardiovascular and all-cause mortality during 40 years of follow-up started among participants with a body mass index (BMI; kg/m^2^) currently accepted within the normal range (from 50th to 74th percentiles).

The need for developing potent treatments for childhood obesity has been recognized for decades and a substantial body of treatment research exists [10–12]. There is also substantial evidence indicating that it is difficult to get more than modest weight loss when treating adolescents with severe obesity [13, 14].

Several reviews and meta-analyses have summarized the results of different childhood obesity treatments and provided recommendations as to which treatments are the most efficacious and which treatment components are predictive of favorable treatment outcomes [11, 12, 15, 16]. Specifically, lifestyle interventions that teach behavioral techniques that focus on incorporating the behavior changes into daily life routines, and are delivered in a family-based format (i.e., targeting both the child and parent), seem to be the most efficacious treatment for childhood obesity [11, 15–18]. However, it is important to note that much of this research has been conducted within efficacy trials. Thus, effectiveness trials, which focus on the applicability and validity of the treatment in usual health care settings with a less selected group of participants, are warranted, as few have been conducted [19].

Childhood obesity treatment of medium-to high intensity and longer duration have been found to be most efficacious [20]. Best effect for treatments that included more than 26 sessions are found in one review [20]. There is however some discussion about how prolonged the treatment needs to be to yield meaningful weight loss outcomes. For instance, one review suggests that interventions that last about four months are as efficacious as treatments of longer duration [21]. A meta-analyses of intervention studies from 2002–2015 [18] finds that weight loss treatment for children has evolved over the past decade, especially in that recent studies report longer duration and follow-up than in the 1990s [18]. Despite these findings that indicate the importance of higher-intensity treatment, many national guidelines for addressing childhood obesity recommend weight surveillance and brief lifestyle counseling in primary care service for children with obesity and their families [22]. However, this approach is not effective, at least not for children and adolescents with severe obesity [22, 23].

Recently, there has been consensus that obesity is a disease [24]. Classifying obesity as a chronic health condition increases the understanding of the fact that extended follow-up after an intensive treatment phase is necessary for weight loss maintenance. Long-term maintenance of treatment effects is a challenge with obesity treatment across both adults and children [25–27]. Family-based behavioral treatments for childhood obesity have, importantly, demonstrated promising long-term effects compared to other treatments [15, 28]. A ten-year follow-up study found that 34 % of the participants who entered the treatment program at age 6–12 had reduced their percent overweight by at least 20 %, and 30 % had BMIs that were no longer in the obese range [28].

Dropout is a substantial concern in treatment of both adult and pediatric obesity [11, 29, 30], but only a limited number of studies have examined the predictors for dropout [29, 31, 32]. Studies show mixed results regarding barriers to treatment participation. Some studies have found higher number of barriers in families who end the treatment program prematurely [32, 33], while another found few differences in degree of barriers among treatment completers compared to non-completers [31]. Post-treatment reported barriers in prior studies include high degree of family stressors, parent-adolescent conflict, lack of time and interest, interference with school schedules, disappointment with amount of weight-loss, and treatment taking place too far from home [31, 32, 34]. Further research on predictors for dropout and barriers to treatment participation, both among non-completers and completers, has important implications for clinical practice [30].

Another subject of clinical importance is to identify pre-treatment factors related to poorer treatment response. Together with knowledge about predictors for dropout and barriers to treatment participation, these factors can identify at risk groups and tailor childhood obesity treatment to increase treatment response. Several pre-treatment factors have been associated with weight loss outcomes in previous research on childhood obesity treatment [30, 31, 35–38], including child age, gender, child initial weight status [36, 38], child mental health problems [36, 37], and parents’ degree of motivation [30, 31, 35, 36]. However, there seems to be a lack of studies investigating the influence of family variables and broader social network support as predictors of treatment response.

The aim of this paper is to describe and explain the design and evaluation of the Family-based behavioral treatment of childhood obesity (FABO)−study targeting children and adolescents with obesity and their families. The description of the study protocol follows the checklist of the CONSORT statement for randomized trials [39] (Additional files 1 and 2).

## Methods/Design

### Intervention

Family-based behavioral social facilitation treatment (FBSFT) is founded on the principles of standard family-based behavioral treatment for obesity, which is the most well documented approach for childhood obesity [11].

FBSFT has an intensive treatment phase including weekly family meetings over 17 consecutive weeks with the same health care worker at the Obesity Outpatient Clinic (OOC), Haukeland University Hospital, Norway. All the health care workers on the multidisciplinary treatment team at the OOC are trained in FBSFT prior to treatment delivery. The multidisciplinary team consists of a pediatrician, nutritionist, physiotherapist, nurse and psychologist. Throughout the study period, the treatment team will have weekly meetings to discuss the patients in addition to monthly supervision sessions with the research team in St. Louis, MO, USA and Pittsburgh, PA, USA through video-conferences.

There are session-specific components and goals for each of the 17 sessions (see Table 1 for complete outline). The treatment targets healthy lifestyle changes in both the children and parents in the areas of diet, physical activity, sedentary activity, sleep and social function. The dietary and physical activity guidance used in the study is based on the Traffic Light Diet [40] in which foods and activities are organized into green, yellow and red groups. Green meaning “go,” yellow meaning “sometimes” and red meaning “limit.” The treatment focuses on implementing the behavior change across all the different settings in the family members’ daily lives (i.e., within the home/family environment, peer network environment, community environment).

**Table 1 Tab1:** Session topics in family-based behavioral facilitation treatment (FBSFT)

Phase	Session	FBSFT Topic
1. Individual and Home Contex	1-2	Introduction to the treatment; plan for the Traffic Light Diet; personalized treatment plan
	3	Healthy and regular eating, communicating with the family about lifestyle changes
	4	Sedentary activity; sleep routines
	5	Physical activity; lifestyle activity
	6	Creating a healthy family and home environment; problem solving skills
	7	Healthy self-instructions; emotions/stress and eating behavior
2. Peer Contex	8	Peers as a support for healthy behaviors (arranging healthy activities with others); assessment of social network
	9	High risk situations (parties, holidays and vacations); prompts for eating and physical activity
	10	A healthy peer environment; communicating with peers about new and healthy habits
	11	Taking on Teasing
3. Community Contex	12	Physical activity and the assessment of RED food in the environment/neighborhood
	13	To be active in your neighborhood; join groups or teams; to elicit support for healthy habits in your neighborhood/environment
	14	To fight weight stigmatization; influences from the media; to build a positive self-image and body image
	15	High risk situations (restaurants and fast food); to focus on healthy habits at school and work
4. Cross-contextual	16	To plan for healthy habits; relapse prevention and consolidating skills across different contexts
	17	Reviewing goals and skills; ending well; planning ahead

Through the treatment sessions, the families are taught a set of behavioral and cognitive techniques for promoting healthy behavior change and dealing with mechanisms that maintain unhealthy lifestyle behaviors:Self-monitoring. Both the parents and children monitor their eating, weight and activity on a week-to-week basic going through the intensive treatment phaseGoal setting, planning and reward systemsStimulus controlEmotion regulation strategiesReframing negative automatic thoughtsCommunication and interpersonal skillsParenting strategiesHealthy modeling from the parentsHealthy methods of self-evaluation and self-assertion

After the intensive treatment phase, the families receive monthly follow-up treatment for 18 months through collaboration between specialty and primary care: monthly follow-up sessions with their school nurse (primary care) and follow-up sessions every third month at the OOC. The focus for these sessions is maintenance of healthy habits.

For families assigned to standard treatment (treatment as usual, TAU), the treatment consists of a post-assessment meeting between a health care worker at the OOC and the family, agreeing on behavioral goals for changing lifestyle, a plan for the implementation of new behaviors and goals for weight loss. Each family also participates in monthly counselling session with their local health care nurse to work on implementing these goals, including measuring their weight change, and also meets every third month for sessions at the OOC for assessments, evaluation of progress and revision of goals. TAU is delivered over the course of 12 months.

### Study objectives and hypotheses

The objectives and hypotheses of the current study are:To evaluate the effect of FBSFT compared to TAU for severe childhood and adolescent obesity in a common health care setting. The primary outcome is weight status, assessed as BMI, BMI standard deviation scores (SDSs) and percentages above the IOTF cut-off for overweight (%IOTF-25) [41]. Secondary outcomes are other weight-related anthropometric measurements (waist circumference (WC) and Waist-to-height ratio (WHtR) and corresponding SDSs), body composition (BIA, DXA), blood test, blood pressure, eating habits, sleep, physical activity as well as psychological well-being and parenting style.○ We hypothesized that FBSFT will be superior to TAU in improving these parameters both during the intensive treatment period and during the follow-up period.
To identify predictors of treatment success and treatment drop out with a focus on family variables, socioeconomic status, social network and mental health.○ We expect children from families in which both parents participate in treatment to demonstrate better weight loss outcome and have lower dropout rate.○ We expect children of parents living together to demonstrate better treatment effects and have lower dropout rate.○ We expect that parental (self-reported) weight status will influence treatment effects and dropout rate; higher BMI category will predict poorer treatment effects and higher dropout rate.○ We expect that lower socio-economic status and limited social network will predict poorer treatment effects and higher dropout rate.○ We expect poorer treatment effect and higher dropout rate among participants with psychological comorbidities.
To evaluate experienced barriers to treatment, and how these factors influence children’s and parents treatment response. Barriers to treatment are classified into four groups: competing activities/life stressors, relevance of treatment, treatment issues (logistics) and critical events.○ We expect lower degree of competing activities/life stressors to predict better treatment response and lower dropout rate.○ We expect higher degree of experienced treatment relevance to predict better treatment response and lower dropout rate.○ We expect lower degree of treatment issues and lower number of critical events to predict better treatment response and lower dropout rate.
To evaluate FBSFT implementation and acceptability for children, parents and health care workers. This is an exploratory study using a brief interview to investigate parents’, children’s and health care workers’ experiences with the treatment.

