### Sample size

One hundred twenty families will be recruited, with 60 families in each treatment arm. Power estimates were calculated using G*Power, version 3.1.3. [42, 43] With two treatment groups (TAU, FBSFT), 3 measurement points (pre-treatment, 6 months post-treatment and 12 month post-treatment) and a correlation of 0.5 between the measurement points, alpha .05, power .80, a small (*f* = 0.10), moderate (*f* = 0, 25) and high (*f* = 0.40) effect size would demand respectively sample sizes of 164, 28 and 12 participants to detect a significant group X time interaction on the primary outcome. For regression analysis of predictors of treatment outcome, a small to moderate effect size is expected (*f* = 0.15), and when testing the increase in R^2^ by adding 1 predictor to an analysis including 5 predictors in total, a sample size of 55 persons will be needed.

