### Anthropometrical measures

Trained assessors at the OOC will measure height and weight for calculation of BMI (kg/m2), WC and body composition (measured with bio impedance (BIA), InBody 720). BMI will be converted to SDS using the extended IOTF [41, 44] BMI references. The percentage of the IOTF 25 threshold (%IOTF-25) is calculated as 100*(BMI/IOTF 25), where BMI is the child’s weight divided by height squared (kg/m^2^), and IOTF 25 is the BMI that corresponds to the IOTF threshold for overweight for the child’s age and sex. Dual-energy X-ray absorptiometry (DXA)-scans for determining the distribution of fat and muscle tissue will be conducted at the Department of Rheumatology at Haukeland University Hospital.

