## Planned data analysis

A two-way MANOVA with one repeated-measure factor (Time: pre-intervention/post-intervention), and one between-group factor (Treatment Group: FBSFT vs. TAU) will be conducted to assess the impact of treatment on primary and secondary outcomes.

A one way within-subjects MANOVA will be used to analyze the effect of time (pre-treatment, post-treatment, 12-, 18-, 24 months post treatment) on primary and secondary outcomes.

In order to identify factors associated with treatment success and treatment drop out, multiple regression analyses will be conducted. The dependent variables are %IOTF-25 and drop-out status (yes/no). The predictors are: both parents participating in treatment, parental marital status, self-reported parental weight, socio-economic status and social network, psychological comorbidities.

In order to identify barriers to treatment and how these barriers influence children’s and parents’ treatment response, multiple regression analyses will be conducted. The dependent variable is %IOTF-25. The predictors are: competing activities/life stressors, relevance of treatment, treatment issues (logistics) and critical events.

Intention-to-treat analyses will be conducted and effect sizes calculated for treatment effects.

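### Three BMI-derived measures share the primary role with none ranked, and the stated pre/post by group MANOVA compares unadjusted change

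*Protocol article*

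**What the plan says.** Under Study objectives and hypotheses, the article gives one primary concept and three measures of it: "The primary outcome is weight status, assessed as BMI, BMI standard deviation scores (SDSs) and percentages above the IOTF cut-off for overweight" (%IOTF-25). No order among them is given.

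Anthropometrical measures shows that the second and third are computed from the first. For the SDS, "BMI will be converted to SDS using the extended IOTF" references. For the other, "The percentage of the IOTF 25 threshold (%IOTF-25) is calculated as 100*(BMI/IOTF 25"), where the denominator is the overweight threshold for the child's age and sex.

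Planned data analysis specifies "A two-way MANOVA with one repeated-measure factor (Time: pre-intervention/post-intervention), and one between-group factor (Treatment Group: FBSFT vs. TAU"), which "will be conducted to assess the impact of treatment on primary and secondary outcomes". No covariate is named. The section does not say whether the three measures form one response vector, whether secondary outcomes join it, or whether each outcome has its own analysis. The regressions in the same section use a single weight outcome: "The dependent variables are %IOTF-25 and drop-out status (yes/no").

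The Sample size section powers one interaction, "to detect a significant group X time interaction on the primary outcome", at three measurement points.

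**The concern.** A confirmatory trial needs one result that decides the question. Here three related measures are declared primary, and the stated method does not resolve them.

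- **Joint reading.** A significant MANOVA says that some combination of the three changed differently between arms. It gives no estimate on a named scale, and it uses three numerator degrees of freedom on closely related information.
- **Separate reading.** There are three tests at .05, with no rule for what happens when they disagree.

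Under either reading, a group-by-time term with two time levels is a comparison of change scores. The baseline value is collected anyway, and using it as a covariate gives a more precise comparison at no cost in data.

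The measure that would most naturally serve as primary also has two descriptions: a percentage above the cut-off in the objectives, and a percentage of the cut-off in the measurement section.

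**Working it through.** **Inputs from the Sample size section:** N = 120 (60 per arm), rho = 0.5 between measurement points, alpha .05, f = 0.10 / 0.25 / 0.40. **Assumed, because the article gives no figure:** the correlation among the three measures, the pattern of effects across them, and no dropout.

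**1. The plan's own figure.** For a group x time interaction on one outcome at m = 3 times, lambda = f²·N·m/(1 − rho), with df1 = m − 1 and df2 = (N − 2)(m − 1).
- f = 0.10, N = 164: lambda = 0.01 × 164 × 3/0.5 = 9.84, power 0.805.
- f = 0.25, N = 28: lambda = 10.5, power 0.812.
- f = 0.40, N = 12: lambda = 11.52, power 0.810.

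The stated 164, 28 and 12 reproduce exactly, for a single outcome. At N = 120 and f = 0.10 the same model gives 66%.

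**2. The stated two-level analysis, one outcome.** With m = 2, lambda = 0.01 × 120 × 2/0.5 = 4.8 on F(1, 118), which gives 58%. This equals (N/4)·D² with D² = 0.16, a standardised change difference of 0.40.

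**3. Joint test on three measures.** Hotelling T² on the three changes uses F(3, N − 4) with lambda = (N/4)·D². If the three carry the same information, D² stays at 0.16, lambda is 4.8 on F(3, 116), and power is 41%.

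*Sensitivity to unequal effects* (60 per arm, difference 0.5 SD, rho 0.5, changes correlated 0.9):

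| Test | Effects across the three measures | Power |
|---|---|---|
| Joint | equal | 64% |
| Joint | 1 : 0.8 : 0.6 | 79.5% |
| Single change score | – | 77.5% |
| Single-outcome ANCOVA | – | 88% |

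So the joint test can overtake a single change score.

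**4. Three separate tests at .05.** The chance that at least one of three null two-sided tests is significant, by simulation, is 9.8% at a test correlation of 0.8, 8.4% at 0.9 and 7.4% at 0.95.

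**5. Baseline adjustment, one outcome.** Per unit outcome variance, a change score has variance 2(1 − rho) and ANCOVA has 1 − rho². The ratio is (1 + rho)/2. ANCOVA power uses F(1, N − 3) with lambda = (N/4)·d²/(1 − rho²). The change-scale effect is held at f = 0.10, where the unadjusted power is 58%:

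| rho | Variance ratio | ANCOVA power |
|---|---|---|
| 0.5 | 0.75 | 71% |
| 0.7 | 0.85 | 65% |
| 0.8 | 0.90 | 63% |
| 0.9 | 0.95 | 61% |

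At rho 0.5, lambda = 30 × 0.16/0.75 = 6.4. At f = 0.25 the joint test, the change score and ANCOVA all exceed 99%.

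**6. The two descriptions of %IOTF-25.** The percentage of the cut-off is 100·BMI/IOTF 25. The percentage above it is that value minus 100. The constant cancels in any change or group comparison, so tests are unaffected, but the reported level is ambiguous.

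**The case against.** The article never says that the three measures form one response vector. Its power calculation is for a single outcome, so one repeated-measures analysis per outcome is a live reading, and under it the three-degree-of-freedom loss disappears. This stands: a reader might infer that the primary test is certainly a joint MANOVA, and the text does not support that.

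A reader might also infer that a single adjusted outcome always has far more power. The documents do not support that either. They give no correlations among the measures and no expected effect. The loss from the joint test depends on the measures carrying the same information. SDS and %IOTF-25 are referenced to age and sex over ages 6–18, so their changes can diverge from change in raw BMI. The ANCOVA gain also fades as rho rises.

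Nor does the article adopt the small effect as its target. It lists N for three effect sizes, so 120 being below 164 does not show that the trial misses its own requirement.

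Finally, a change comparison is valid in a randomised trial, and covariates are often left to an analysis plan. The first half is right: baseline adjustment is a matter of precision, not a correction of bias. The second half does not dispose of the point, because the article states a specific method whose interaction is unadjusted. Nor does it reach the primary outcome, which the article fixes as three unranked measures.

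**Conclusion.** The point holds in a limited form. No measure is designated to decide the trial, and that defect survives both readings of the MANOVA. Its consequence is either a result without an effect on a named scale or, if any one of three tests suffices, a familywise error of about 8% (7.4% to 9.8% over assumed test correlations of 0.95 to 0.8).

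The power consequences are conditional. The fall from 58% to 41% requires the joint reading, f = 0.10, rho 0.5 and equal information in the three measures. The rise from 58% to 71% by baseline adjustment applies under either reading, but at the plan's rho of 0.5 and f = 0.10. None of this matters in practice at f = 0.25. The two descriptions of %IOTF-25 are a reporting ambiguity only.

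**What to change.** By a documented amendment before unblinding:

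- Name one primary measure. %IOTF-25 is the natural candidate: it is referenced to age and sex, and it is already the only weight outcome in the planned regressions.
- Test it at .05 by ANCOVA, or by a mixed model, with its own baseline value as covariate.
- Make BMI SDS and BMI supportive, and keep the secondary outcomes outside the primary test.
- Use one definition of %IOTF-25 throughout, either of the cut-off or above it.

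No visits, measurements or families are added. The cost is more than wording, however. Enrolment began in January 2014, so this changes a declared primary outcome in a running trial and must be dated and justified. The Blinding section keeps the data manager and statisticians blinded until analysis, which leaves room to do it cleanly. The sponsor also gives up the option of claiming success on whichever weight metric looks best.
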